### Statistics

The effect of the intervention on attendance will be estimated by the difference of the proportion of citizens attending each of the groups. Furthermore, a descriptive analysis of attendees and non-attendees will be performed regarding sex, age, smoking history, self-reported lung symptoms, and spirometry measurements. The analysis will follow the intention-to-treat principle [16].

For the descriptive part of this study, bivariate and multivariate analyses will be performed. Numerical variables are presented as mean ± standard deviation, and binary variables as absolute numbers and relative (percent) frequencies. Student’s *t* test will be used when comparing means or changes in means of numerical variables, and Fisher’s exact *t* test or the chi-squared test will be used when comparing proportions for binary variables. Binary outcomes will be analyzed with logistic regression. The statistical significance level is set at *p* < 0.05. Statistical analysis will be performed using Stata 14.0 software [37]. A detailed Statistical Analysis Plan will be finalized before access to the data and will be attached to the ClinicalTrials.gov trial identifier (NCT02615769).

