## Background

Early detection of lung diseases can help reduce the severity of these diseases when inflicted. Lung diseases are among the most frequently occurring and serious conditions in the western world, including Denmark [1]. The Danish Health Authority recommends spirometry every second year to all individuals older than 35 years with at least one respiratory symptom and/or exposure to any known risk factor (smoke, genetics, air pollution, chemical fumes, or dust) in order to facilitate early case finding of chronic obstructive pulmonary disease (COPD) [2]. However, an estimated 200,000 Danish citizens (50%) with COPD remain undiagnosed and unknown to the health care system [2, 3].

Preventive health checks including spirometry can be used to detect lung diseases at early stages. However, a well-known challenge is low uptake, especially in people at risk of developing disease [4]. Previous studies of attendees in preventive health checks [5] reported average attendance rates from 18 to 82%. They also showed that non-attendees were less healthy than the attendees and that those least likely to attend health checks were younger, single men with low income or low socioeconomic status, active smokers, or the unemployed or less educated [5]. Little is known about what motivates the attendance to health checks.

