### National registers

In Denmark we have a unique opportunity to link study measurements to nationwide medical registers and databases [21, 22]. To understand the processes involved in responding to the intervention, especially among the non-attendees, secondary characteristics regarding sociodemographics, redeemed medication, and consultations at their general practitioner will be obtained by linking to Danish registers [21, 30, 31].

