### Randomization

Randomization is performed on clusters defined by households based on addresses from the Danish Civil Register [21, 22]. Furthermore, the randomization is balanced at the general practitioner (GP) level to ensure distribution of the follow-up workload over 5 years. Using the same index individual per households, 4356 citizens randomized to group 4 in the CHPP are further randomized by household into two parallel groups: intervention or comparison (Fig. 1). Randomization is handled by an independent statistician. Implementation and booking are handled by a data manager. The intervention, the outcome, and the group assignment are not revealed to the participants, And the health care professionals also remain blinded. The blinding will be unlocked as the last spirometry measurement is done in December 2016.

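### Attendance effect is stated as a plain difference in proportions with no covariate or household term; a prespecified adjusted, household-clustered risk difference would add a little precision at almost no cost

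*Protocol article*

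**What the plan says.** On the attendance outcome the Statistics section says: "The effect of the intervention on attendance will be estimated by the difference of the proportion of citizens attending each of the groups". No covariate, practice term or household term is attached to it.

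The next paragraph opens: "For the descriptive part of this study, bivariate and multivariate analyses will be performed". It then lists t, Fisher and chi-squared tests and adds: "Binary outcomes will be analyzed with logistic regression". That sentence neither mentions attendance nor names covariates. The section closes by deferring detail: "A detailed Statistical Analysis Plan will be finalized before access to the data".

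Three other places bear on the point:

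- **Predictors.** The Background reports from previous studies that "those least likely to attend health checks were younger, single men with low income or low socioeconomic status", and adds smokers, the unemployed and the less educated.
- **Availability.** Under Population, the civil register identifies everyone eligible by age. Under Statistics, attendees and non-attendees are to be described by sex and age. Under National registers, sociodemographic data, medication and GP contacts "will be obtained by linking to Danish registers", with non-attendees particularly in mind.
- **Balance by practice.** Under Randomization, "the randomization is balanced at the general practitioner (GP) level to ensure distribution of the follow-up workload over 5 years".

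**The concern.** The trial compares attendance between two groups in which every randomized citizen has an observed outcome, and in which age and sex are known for all. Several further predictors of attendance can be had from registers that the trial already plans to use. A comparison that leaves this information out is valid, but its interval is somewhat wider than the same data allow.

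There is also a question of scale. The target is 5 percentage points. If the logistic regression sentence covers attendance, the default output is an odds ratio. With covariates in the model, that odds ratio is a conditional one and does not answer the percentage-point question directly. The text does not say how the difference in proportions and the logistic model relate, or which carries the conclusion.

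Finally, the unit of randomization is the household, yet none of the methods listed under Statistics mentions it.

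**Working it through.** **Inputs from the Sample size section:** 53% against 58%, two-sided alpha 0.05, power 0.90, 1:1 allocation, design effect 1.05, total 4356 (2178 per arm). The share of attendance variance explained by covariates (R²) is not in the document and is treated as an assumption.

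**Step 1: the plan's own figure.** With pooled variance under the null and mean proportion 0.555:

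n per arm = [1.960 × √(2 × 0.555 × 0.445) + 1.282 × √(0.53 × 0.47 + 0.58 × 0.42)]² / 0.05² = 2074.

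2074 × 1.05 = 2177.7, so 2178 per arm and 4356 in total. The stated size is reproduced exactly.

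**Step 2: precision without adjustment.** SE = √[(0.2491 + 0.2436) × 1.05 / 2178] = 0.0154. The 95% half-width is 1.96 × 0.0154 = 3.02 percentage points, and power is 90.0%.

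**Step 3: a plausible R².**

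- Practice: the Sample size section puts the practice intra-cluster correlation at about 0.01, so practice explains about 1% of the variance.
- Sex and age: for an attendance gap d_s between equally frequent sexes and a linear gap d_a across a uniform age range of 30 to 49, R² = (d_s²/4 + d_a²/12) / (0.555 × 0.445). With d_s = 0.05 and d_a = 0 this is 0.3%. With d_s = 0.15 and d_a = 0.20 it is 3.6%. Both gaps are assumptions.
- Together: 1% + 0.3% = 1.3% to 1% + 3.6% = 4.6%, rounded to a range of 1% to 5%. A value of 10% is kept as an optimistic ceiling that also allows for register variables such as income and education.

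**Step 4: effect of adjustment.** The inflated variance is multiplied by (1 − R²). This approximates both linear adjustment and standardization after a logistic model.

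| Assumed R² | Power at N = 4356 | 95% half-width (points) | Total N for 90% power |
|---|---|---|---|
| 0 | 90.0% | 3.02 | 4356 |
| 1% | 90.3% | 3.01 | 4312 |
| 2% | 90.6% | 2.99 | 4270 |
| 5% | 91.4% | 2.94 | 4138 |
| 10% | 92.8% | 2.87 | 3920 |

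For 1% to 5%, the gain is 0.3 to 1.4 points of power, at most 3.02 − 2.94 = 0.08 points of half-width, and the equivalent of 4356 − 4312 = 44 to 4356 − 4138 = 218 citizens.

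**Step 5: cross-check.** A rough simulation used 600 runs, 46 practices, practice correlation 0.01, allocation balanced within practice, a sex gap of 10 points, an age gap of 15 points and no further correlation within households. The empirical SE was 0.0148 both without and with adjustment. This agrees with a very small gain. It did not include the register variables.

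**Step 6: comparison with household clustering.** At 1.5 citizens per household, a design effect of 1.05 corresponds to a household correlation of 0.05/0.5 = 0.10. If the design effect were 1.15 (correlation 0.15/0.5 = 0.30), crude power would be 87.2%, and 88.8% with R² of 5%. At 1.25 (correlation 0.25/0.5 = 0.50), the figures are 84.4% and 86.2%. Adjustment recovers only part of such a loss, and it does not correct a standard error that ignores households.

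**The case against.** The strongest case for leaving the text alone has four parts.

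**The statistical analysis plan may settle it.** The article defers detail to a plan that is not shown, and a covariate list normally belongs there. This largely stands: the absence of a list in a condensed article is not a fault. What remains is that the article does state an estimator for attendance and confines multivariate work to the descriptive part. Its one sentence on regression leaves the scale open.

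**The text does not exclude adjustment.** A reader might infer that the main analysis is certain to be unadjusted. The document never says so. Attendance is binary, so the logistic regression sentence may apply to it, and a standardized risk difference is itself a difference in proportions. This stands.

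**The role of practice is unclear.** A reader might infer that the two-arm comparison drops a factor on which its randomization was balanced. The document does not show this. The reason given for balance is workload over 5 years, which belongs to the parent five-group allocation. The second step is described, in the text and in the legend of Fig. 1, only as randomization by household. If the arms were in fact balanced within practice, the crude estimate already benefits, and only a standard error that ignores practice would be slightly too wide.

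**The crude difference is valid and the gain is small.** Both are true. Chance imbalance is already covered by a correctly computed crude interval, and planned power is already 90%. A reader might infer biased or seriously underpowered results; nothing here supports that.

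**Conclusion.** The point holds as a low-cost improvement, not as an error. The estimator stated for attendance is a simple difference in proportions with no covariate or household term named. The logistic model mentioned beside it has no stated covariates and would by default report on another scale. The crude difference remains an unbiased intention-to-treat estimate.

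The benefit depends on an R² that the document does not give. At 1% to 5% it is worth roughly one point of power and less than a tenth of a percentage point of half-width; even the 10% ceiling adds only 92.8% − 90.0% = 2.8 points of power. These figures also take the stated design effect of 1.05 as given.

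The main reasons to act are that the change costs almost nothing and that the same paragraph would settle the scale of the result and the treatment of households. The household allowance matters more for valid inference than the covariates do.

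**What to change.** Before data access, write into the statistical analysis plan, or confirm that it already contains, the following:

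1. **Main attendance analysis:** a logistic model with arm, age, sex and a short named list of pre-invitation register variables (for example cohabitation, education and income), plus practice. Practice enters as a balancing factor if the two-arm randomization was balanced on it, and otherwise as an ordinary covariate. State which of the two applies.
2. **Reported effect:** the marginal risk difference in percentage points, standardized over all randomized citizens, with 95% CI and standard errors clustered on household. This keeps the 5-point target as the quantity estimated.
3. **Supporting analysis:** the crude difference in proportions, also with household-clustered standard errors.
4. **Covariates to leave out:** smoking and lung symptoms from the questionnaire, since these are collected from participants before the health check and are not available in the same way for non-attendees.

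The cost is one paragraph and no new data collection. Register linkage is already planned; it would need to cover attendees and non-attendees in both arms. The covariate list must be fixed before group assignment is unlocked, so that there is no later choice among models.

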## Discussion

This study is the first to examine the benefits of a low-cost and enhanced invitation strategy to identify lung impairment among young adults in a real-world setting. It is designed as a pragmatic and randomized study and will provide information which can be used directly by health care planners in the decision of how to implement health checks. The outcomes were chosen to mirror the aims of the intervention: the overall attendance rate and the attendance of people at risk for lung impairment.Our recruitment strategy is to reach the citizens in three different ways: by webpage, leaflet, and invitation letter in a randomized controlled design. Prior studies have shown an increase in attendance by enhancing invitation material [9, 11, 12, 38]. Therefore, we expect an increase in the attendance of 5 percentage points, and we also expect that more people at risk will attend. We believe it is a realistic goal, even though previous studies indicate that smokers feel ashamed and guilty of their self-inflicted disease and therefore hesitate to seek help [4]. In order to avoid having smokers absent themselves, when we were designing the new material for the intervention group, we involved a communications consultant from the Danish Lung Association [39], who is an expert in content and comprehensibility.

### Strengths and limitations

Participants will be enrolled directly from the general population; therefore, they will not receive any screening prior to inclusion. Thus, the generalizability will not only reflect certain at-risk populations such as current smokers, prior smokers, or citizens with chronic disease. The high transferability of the invitation material and the application of the intention-to-treat principle provide a high external validity. Moreover, the objective measure of attendance contributes with a high internal validity. We chose cluster randomization by household to limit the expected contamination between attendees living together, because motivation to attend a health check will potentially impact the entire household. To avoid having attendees refuse to participate, households are invited together and two reminders are sent out. Furthermore, appointments are scheduled outside of work hours. Finally, we have the unique opportunity to use the Danish registers as a population-based health care database with information about the non-attendees [21].

The present study has some limitations. Firstly, we are aware that both groups have the same accessibility to the webpage regarding how to prevent lung disease, and this may dilute the difference between the two groups. Secondly, the right level of extra information is difficult to achieve. Too much information may cause the participants to believe that the study is only about lung function and possibly scare some of the citizens at risk. On the other hand, too little preventive information may dilute the intervention. Thirdly, we have no spirometry measurements on the non-attendees, which complicates the comparison among the non-attendees and the attendees. Nonetheless, we have the opportunity to supply the characteristics of the non-attendees by redeemed medication and sociodemographic characteristics by the Danish registers [21, 31]. Although our population is fairly young, the most severely affected and chronic patients will not show up for the examination as it requires some physical and mental effort, but we expect the effect to be equal among the two groups. Finally, there is a risk of misclassification among, e.g., citizens with flu or pneumonia, thus resulting in false positive outcomes. However, this risk is expected to be equal among the two groups due to the randomization.

### Perspectives

Lung diseases represent a significant burden for patients and health care systems worldwide. Optimizing early detection followed by pharmacological and non-pharmacological interventions can not only improve a patient’s health status and quality of life, but can also reduce health care expenses. The results from the present study are expected to contribute important knowledge about the value of information on spirometry in invitations to health checks.

### Trial status

At the time of submission of this manuscript, the trial has enrolled approximately 3500 participants. Recruitment is ongoing.

## Abbreviations

CHPP: Check your Health Preventive Program
CPR: Civil personal registration
CRS: Danish Civil Registration System
FEV_1_: Forced expiratory volume in one second
FVC: Forced vital capacity
GP: General practitioner
RCT: Randomized controlled trial
